### Randomisation

Selected villages will be allocated to either the intervention or control arm using a 1:1 ratio through a transparent, non-computer-based ceremonial randomisation procedure. Randomisation will be conducted during official public meetings at the District Offices of Pong Nam Ron and Soi Dao; therefore, it will be restricted to the district level for operational feasibility. A total of 24 identical, opaque, sealed envelopes will be prepared in advance and used for allocation (intervention or control) by a member of the trial coordination team not involved in recruitment, enrollment, or intervention delivery. During the ceremony, Village Heads will draw sealed envelopes containing the pre-prepared allocation assignments. To maintain transparency and stakeholder engagement, Village Heads will draw one envelope each in the presence of the trial team, other Village Heads, VHV Heads, and District Chiefs. The allocation will be revealed after the VHVs in each arm have provided informed consent for participation in the trial. The allocation results will then be securely transmitted to the central trial data management team.

### Blinding criteria

Blinding will be implemented where feasible, considering the community-based nature of the intervention. Due to the design, it will not be possible to blind VHVs, participants, or the local trial team to allocation status. Outcome assessors will be blinded to the intervention allocation. Data analysts, including the statistician, principal investigator, and trial supervisors, will also remain blinded to allocation until completion of the primary analysis. The data manager will not be blinded, as access to allocation information is required for data linkage and management. Details of blinding implementation are provided in Table 1.

**Table 1 pone.0354989.t001:** Implementation of blinding in the Saan Suk cRCT (ticked box indicates blinding to the information).

Data	Local Participants and Facilitators					Local Trial Team		Trial Coordination Site Team			
	Village Head	VHV	Household head	Respondent	VHV trainers	Leading team*	Outcome assessors	Data manager	Statistician	Trial PI	Trial supervisors
District									x	x	x
Village name									x	x	x
Village location, address									x	x	x
Village Head name									x	x	x
House address									x	x	x
Household head name									x	x	x
Respondent name									x	x	x
VHV name									x	x	x
Generated District ID	x	x	x	x	x		x				
Generated Village ID	x	x	x	x	x		x				
Generated Household ID	x	x	x	x	x		x				
Generated Respondent ID	x	x	x	x	x		x				
Village Health Volunteer ID	x	x	x	x	x						
Intervention allocation							x		x	x	x
Masked allocation	x	x	x	x	x		x				

*Leading team in Thailand: field supervising manager, leading investigators from Khon Kaen University.

Routine unblinding will not occur during the trial. All outcome assessments and primary statistical analyses will be conducted with masked allocation, and the study database will remain blinded until database lock and completion of the prespecified primary analyses. Unblinding before database lock will be permitted only under exceptional circumstances in which knowledge of intervention allocation is required for ethical, regulatory, or legal reasons.

### Informed consent

We will obtain informed consent from four groups: Village Heads, Village Health Volunteers (VHVs, including VHV Heads), Household Heads, and adult household members selected for the outcome assessment. All individuals will receive a participant information sheet and will have the opportunity to ask questions before providing consent. Informed consent from Village Heads, VHV Heads, and VHVs will be obtained by the research team before the allocation of interventions. Village Heads will provide consent for their villages to participate in the study before randomisation. In the intervention arm, household members will provide informed consent before the intervention implementation. In the control arm, individuals participating in the outcome assessment will be asked to provide informed consent before the procedure.

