Following the village and VHV Head enrollment, we will return to the villages to explain the meeting outcomes and the study implementation to the randomly selected VHVs from the registry and obtain their agreement to participate in the study using informed consent procedures. Participating VHVs will provide information on the households they are usually responsible for, including the number of people in each household, the number of eligible adults, their ages, and names. This data will serve as a sampling frame for the random selection of seven households to participate in the trial procedures. The number of households that a VHVs regularly visits can range from 7 to 15. The data manager in the coordination site will receive a digitised list of household IDs, including the names and ages of the adults. The data manager will then randomly select seven households for participation using a pre-developed function in *R* software that facilitates random selection of the needed number from the provided sequence, i.e., 7 from n = 1–15. The data manager will provide an additional two households for replacement in case the selected household does not agree to participate. VHVs will inform them about the study and obtain verbal consent to participate in the trial.

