### Statistical analyses

The statistical analysis will follow the intention-to-treat (ITT) principle. All eligible and consenting household members selected for outcome assessment will be analysed according to the randomised allocation of their village, regardless of intervention exposure, adherence, protocol deviations, or withdrawal from intervention activities. The village is the unit of randomisation, while outcomes are measured at the individual participant level. All analyses will therefore account for clustering at the village level. The allocation groups will remain masked to the statistician where feasible, until the primary analysis code and outputs are finalised. The primary comparison will be between villages allocated to the Saan Suk intervention and villages allocated to the current practice. All effect estimates will be presented with 95% confidence intervals. Statistical significance will be assessed using two-sided tests with an alpha level of 0.05.

A per-protocol analysis will be conducted as a sensitivity analysis. Here, we will include participants in intervention villages who received at least three or four planned visits, and participants in control villages with no documented exposure to Saan Suk-specific materials or training content.

Baseline characteristics will be summarised by cRCT arm to assess the comparability of the randomised groups and to describe the study population. Because randomisation is conducted at the village level, baseline balance will be assessed at both the cluster and individual levels. Cluster-level baseline characteristics include sub-district, distance to neighbouring study villages, number of registered VHVs, and relevant ecological characteristics, i.e., land use classes (e.g., vegetation, agricultural areas) and land-use interfaces where contact between people and wildlife may occur. Individual-level baseline characteristics will include age, sex, education, income, occupation category, household size, prior experience of zoonotic infectious diseases, and prior awareness of zoonotic diseases. The baseline assessment of the outcomes will not be conducted due to restricted operational feasibility. The background characteristics will be presented as means and standard deviations or medians and interquartile ranges for continuous variables, and as counts and percentages for categorical variables. Cluster size variation will be described and considered in sensitivity analyses.

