**ENROLLMENT:**												
Eligibility check, selection of villages and VHVs	x											
Scoping visits and stakeholder engagement	x											
Enrollment of villages, Informed consent (Village Heads)		x										
Enrollment of VHVs by VHV Head and Village Heads, Information sheet and consent		x										
Enrollment of households by VHVs, Verbal informed consent			x	x								

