**RANDOMISATION:**												
1:1 random allocation of villages to intervention and control		x										

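### Households are enrolled after allocation by VHVs who know their arm, and individual consent is timed differently by arm, so the analysed sample is exposed to post-randomisation selection

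*Protocol article*

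**What the plan says.** Consent before allocation covers only leaders and volunteers: "Informed consent from Village Heads, VHV Heads, and VHVs will be obtained by the research team before the allocation of interventions" (Informed consent). The condition for opening the allocation is the same: "The allocation will be revealed after the VHVs in each arm have provided informed consent for participation in the trial" (Randomisation). Table 2 places "1:1 random allocation of villages to intervention and control" in week 1.

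Households come next. The data manager draws seven per VHV, plus two replacements, from lists that the VHVs supply; then "VHVs will inform them about the study and obtain verbal consent to participate in the trial" (Recruitment). Table 2 lists "Enrollment of households by VHVs, Verbal informed consent" in weeks 2 and 3. On blinding, the plan states that "it will not be possible to blind VHVs, participants, or the local trial team to allocation status" (Blinding criteria).

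Individual consent differs by arm. In the intervention arm it is taken before delivery starts. For controls: "In the control arm, individuals participating in the outcome assessment will be asked to provide informed consent before the procedure" (Informed consent). The outcomes section adds that the trial team takes any outstanding consent at the interview session.

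The analysis set is defined as follows: "All eligible and consenting household members selected for outcome assessment will be analysed according to the randomised allocation of their village" (Statistical analyses). The same section says that outcomes are not assessed at baseline.

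**The concern.** Randomising villages makes the arms comparable in expectation for everyone who could have been sampled. That protection carries through to the analysis only if the analysed people are fixed before allocation is known, or are recruited in a way that allocation cannot influence. Here neither condition is met. The recruiter knows the arm, the household may know it, refusals are replaced at that stage, and individuals agree to different things at different times: a four-week visit programme in one arm, a single interview in the other.

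If willingness to take part is related to knowledge, and differs by arm, the two samples will differ in knowledge before any effect of the programme. The primary endpoint is a post-intervention score only, so such a difference would be read as part of the treatment effect.

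**Working it through.** **Step 1. Order of events**

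| Event | When | Source |
|---|---|---|
| Village Head and VHV consent | Week 1, before allocation | Informed consent; Table 2 |
| Randomisation | Week 1 | Table 2 |
| Reveal | Once VHVs have consented | Randomisation |
| Household enrolment and replacement by VHVs | Weeks 2-3 | Recruitment; Table 2 |
| VHV training, intervention arm | Week 3 | Table 2 |
| Individual consent, intervention arm | Before delivery starts, 17 August | Informed consent; status and timeline |
| Individual consent, control arm | At the interview, 14-30 September | Informed consent; status and timeline |

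From 17 August to 14 September is 28 days, so the two consent points lie at least four weeks apart.

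**Step 2. Statements that do not fit together**

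- Ethical considerations has every participant giving written consent before enrolment. Recruitment and Table 2 have verbal consent for households, and Informed consent lets control individuals consent at the interview.
- Table 2 collects baseline variables of household members in week 3 with no restriction by arm. Under the Informed consent section, control individuals have not yet consented then.

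**Step 3. Precision of the comparison**

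Inputs from the sample size section: SD 15.23, ICC 0.028, 12 villages per arm, 42 participants per village, d = 0.40, 15% attrition.

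- Target difference: 0.40 x 15.23 = 6.09 points, the plan's approximately six.
- Total: 24 x 42 = 1,008, as stated. The usual formula gives 132 per arm; x 2.148 (design effect, 1 + 41 x 0.028) = 283.5; / 0.85 = 333.6; x 1.05 = 350.3, or 9 villages of 42. The plan chooses 12 and cites operational feasibility, so the larger number is no error, and it does not affect this point.
- SE of the arm difference = SD x sqrt(2 x [1 + (m - 1) x ICC] / (12 x m)).
  - m = 42: 15.23 x sqrt(2 x 2.148 / 504) = 1.41.
  - m = 42 x 0.85 = 35.7: 15.23 x sqrt(2 x 1.9716 / 428.4) = 1.46.

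**Step 4. What a selection shift would do (assumed inputs)**

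If a share f of people is lost from one arm only, and they score g points below those retained, the arm difference shifts by f x g. The plan gives neither f nor g. Examples:

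- f = 10%, g = 0.3 SD: 0.10 x 0.3 x 15.23 = 0.46 points
- f = 20%, g = 0.3 SD: 0.20 x 0.3 x 15.23 = 0.91 points
- f = 20%, g = 0.5 SD: 0.20 x 0.5 x 15.23 = 1.52 points

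Type I error with no true effect is the two-sided rejection probability of a noncentral t with 24 - 2 = 22 degrees of freedom and noncentrality shift/SE:

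| Shift (points) | SE 1.46 | SE 1.41 |
|---|---|---|
| 0 | 5.0% | 5.0% |
| 0.5 | 6.2% | 6.3% |
| 1.0 | 10.0% | 10.5% |
| 1.5 | 16.6% | 17.5% |

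A normal selection model gives a wider range. With non-participation of 5% in one arm and 15% to 30% in the other, and a correlation of 0.1 to 0.5 between willingness and knowledge, the shift is about 0.25 to 3.0 points. A larger sample shrinks the SE but leaves the shift unchanged.

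**The case against.** The plan has real safeguards. Households are drawn at random by the data manager, with the same reserve in both arms. Verbal household consent is taken in weeks 2-3 by the same procedure in both arms, so the difference in timing concerns individual consent only. Rates of selection, consent, refusal and non-response are to be compared by arm and cluster, expressly to assess selection bias. The primary model adjusts for age group, sex, education and occupation, and further covariates can be added on imbalance. Established VHV relationships and compensation may keep refusals few.

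All of this stands, and it rules out several stronger readings that a reader might infer:

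- *That control respondents are simply whoever attends.* The outcomes section assesses recruited household members in both arms.
- *That VHVs take control respondents' individual consent.* Outstanding consent is taken by the trial team; the unblinded VHVs enrol households.
- *That nobody selects the adult to be interviewed.* The Informed consent section speaks of adults selected for the assessment. A condensed article may leave the method to the full protocol.
- *That the bias could be neither seen nor adjusted for.* Differential refusal would show in the planned comparisons, and selection on measured covariates would be partly adjusted.

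The safeguards still leave a gap. The random draw does not govern who agrees or who is replaced. Comparing refusal rates describes a problem without correcting it. Covariates do not capture interest in the topic or prior knowledge, and no baseline score stands in for them.

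**Conclusion.** The point holds as a structural risk of selection bias in the primary comparison. It rests on the sequence in Table 2, the condition for the reveal, the arm-specific rule for individual consent, and an analysis set conditional on consent. It is not evidence that bias will occur.

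Size and direction are unknown. Selection towards more interested intervention households would inflate the effect; the opposite would mask it, and a 1.5-point shift is 1.5 / 6.09 = 25% of the target difference. The rise in type I error to roughly 6% to 17% is an illustration for shifts of 0.5 to 1.5 points. It ignores whatever covariate adjustment would absorb. The documents do not support citing it as an expected bias or assuming that it favours the intervention.

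The issue deserves action because it concerns the primary endpoint, the change is procedural, no participant had been enrolled at submission, and it cannot be repaired after enrolment. The conflicting consent statements need reconciling in any case.

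**What to change.** 1. After VHV consent, obtain the household lists. Have the data manager draw and lock the seven households, the two replacements and one named adult per household before allocation is revealed.
2. Take individual consent for the outcome interview in both arms in the same pre-intervention window, with the same form and procedure, and before the reveal where feasible.
3. Use replacement households only before the reveal. Count later refusals as missing outcomes.
4. Define the intention-to-treat set as all adults on the locked list, with non-participants handled under the existing missing-data plan.
5. Reconcile Ethical considerations, Informed consent, the outcomes section and Table 2 on who consents, when, and whether verbally or in writing, including the basis for collecting baseline variables in week 3.

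**Cost.** The reveal moves about one week, to the end of week 2. It cannot easily move further, because intervention VHVs are trained in week 3 and community meetings run in weeks 3-4. Household enrolment is therefore compressed into week 2, or training and meetings shift slightly. If full consent before the reveal proves impracticable, locking the list first and using one consent window still removes much of the exposure. No extra staff are needed. Recruitment, Randomisation, Informed consent, Primary and secondary outcomes, Statistical analyses, Ethical considerations and Table 2 need amending.

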### Intervention and comparator

The Saan Suk is a community-based One Health educational programme designed to be delivered by trained VHVs during routine household visits in rural Thailand. It was co-developed with community stakeholders in rural Thailand, including Village Heads, VHVs, and community members, using the HCD approach [32]. Community input and feedback guided the development of the intervention materials, delivery format, culturally appropriate content, and field feasibility considerations during the design and pilot phases. The Saan Suk programme is multimodal and includes community engagement, educational videos, leaflets, calendars, and practical items, including soap, biodegradable gloves, wet tissues, and cutting boards, used as learning tools to be delivered by VHVs to introduce and reinforce key information and support preventive behavioural practices. Household members will receive intervention materials comprising nine illustrated leaflets and three animated videos covering One Health topics, such as zoonotic diseases and spillover, forest and wildlife protection, market safety, safe food preparation, and how to safely handle livestock, bats, and wildlife. These materials complement the explanations and discussions provided by the VHVs and can be revisited by household members after the visits (see examples of the pamphlets in S2 Fig). All materials are culturally adapted, use plain language, and depict familiar community settings and daily life situations encountered in rural Thailand.

Different modes of the Saan Suk programme serve distinct but complementary functions integrated into each visit: 1) videos and leaflets establish risk identification and knowledge of transmission mechanisms; 2) practical demonstrations and handouts of protective items build self-efficacy and behavioral skills by providing tangible, actionable strategies; 3) calendars and take-home artefacts (such as cutting boards reinforcing food separation practices) serve as environmental cues and reminders that extend learning beyond the visit, supporting habit formation and maintenance of safer behaviours; and collectively, 4) these materials articulate the benefits of protective actions through concrete, contextualised examples relevant to household and agricultural settings (Fig 2).

**Fig 2 pone.0354989.g002:**
[figure not shown]
Schematic representation of the Saan Suk intervention components.

By combining informational, behavioural, and motivational elements across multiple modalities, the materials address the sequential pathway from risk awareness to behavioural intention and the adoption of sustainable practices. Adherence to the intervention will be supported through existing community health structures, structured supervision of VHVs, and endorsement by the Chief of District and provincial health authorities. VHVs maintain established relationships with households through routine visits, which is expected to facilitate engagement and continued participation in the intervention. VHV participation in the study will be limited to VHVs who are active in their role and willing to engage in training and all study procedures. Engagement of Village Heads will further support adherence at the community level, as their endorsement of the study and facilitation of the Saan Suk activities are expected to promote participation and sustained engagement among households. Intervention delivery will be monitored through activity logs maintained by VHVs, including records of household visits, dates, and relevant observations. The research team will also record attendance at training sessions. These records will be used to assess adherence to the intervention protocol and identify any deviations. VHVs and participating household members will receive modest financial compensation for their time and participation, in accordance with local standards.

We will compare the co-designed Saan Suk intervention with the current practice. Current practice refers to the usual household visits and routine health information provided by VHVs who have received standard training but have not undergone Saan Suk training. The comparator was selected to reflect real-world conditions and to estimate the incremental effect of the Saan Suk intervention beyond standard community-based health communication. To minimise contamination, control clusters will not be exposed to Saan Suk-specific materials, messages, or training content. Participation in the Saan Suk trial does not restrict access to usual health care, routine VHV services, or other public health programmes normally available in the community.

As this trial involves a non-clinical educational intervention, no medical risks are anticipated. However, criteria are defined for discontinuing or modifying the allocated intervention at the individual, provider, and trial levels. For households and individuals, we will discontinue (stop all remaining study visits for that household) if any of the following occur: (1) participant or household head requests to stop participation at any time, for any reason (no justification required); (2) any safety event during or within 24 hours after a visit that poses immediate risk to the participant, household member, or VHV (e.g., physical aggression, threats, severe dog bite or animal attack, hazardous environment); (3) serious adverse event plausibly related to the visit (e.g., injury while acting on a demonstration); (4) confidentiality concern that cannot be mitigated; and (5) loss of eligibility, such as when a participant moves away or lacks capacity to consent. Discontinuation may also occur following a request from VHVs, community leaders, or local authorities. At the VHV level, the intervention delivery will be discontinued if any of the following occur: (1) the VHV fails competency checks after training, (2) breaches confidentiality, or (3) is implicated in a safety-related complaint. In such cases, households will be reassigned to another trained VHV within the same village where feasible. If reassignment is not possible, the intervention will be modified (e.g., delivered in leaflet-only format by a supervisor) or discontinued, and this will be documented as a delivery limitation rather than a crossover.

At the trial level, cRCT may be discontinued (1) in case of major logistical, environmental, political, and civil unrest barriers preventing continuation of the study procedures, (2) ethical or safety concerns raised by the Ethics Committee or relevant authorities, or (3) external events such as natural disasters or public health emergencies that make study implementation unsafe. Discontinuation may also occur if there is (4) an inability to enrol or retain clusters or participants at a sufficient rate to ensure trial completion, (5) loss of implementing partners or VHV network capacity, or (6) data quality failure compromising interpretability, such as when more than 20–30% of primary outcome data are missing.

